##### Attribution criteria for adverse events

2.9.3.2

To differentiate between adverse events (AEs) causally related to acupuncture intervention and those potentially attributable to pre-existing post-stroke depression (PSD), attribution will be determined in accordance with the CIOMS guidelines (45) and the Standards for Reporting Adverse Events in Acupuncture Clinical Trials (46). Detailed criteria are provided in Table 3.

**TABLE 3 T3:** Severity grading criteria for adverse events.

Severity grade	Core definition	Diagnostic criteria
Mild	Symptoms are mild and do not affect daily life or trial participation	1. Local symptoms: Such as mild soreness at the acupuncture site, transient throat numbness and distension (duration < 30 min); 2. Functional impact: No restrictions on daily activities; able to complete interventions normally; 3. Management requirements: No special treatment needed; symptoms resolve spontaneously.
Moderate	Symptoms are noticeable and may moderately interfere with daily activities or trial procedures; they are amenable to symptomatic treatment.	1. Local symptoms: Such as persistent throat discomfort for 1–2 h after acupuncture, or local skin erythema with a diameter of 2–3 cm; 2. Functional impact: Need to adjust daily activities (e.g., reduce intake of hard foods) but without affecting intervention implementation; 3. Management requirements: Symptomatic treatment required (e.g., lozenges for soothing the throat) and symptoms are alleviable.
Severe	Symptoms are severe and significantly affect daily life or result in inability to continue the trial	1. Local symptoms: Such as severe laryngospasm (duration > 10 min) after acupuncture, or skin redness and swelling with a diameter > 3 cm accompanied by pain; 2. Functional impact: Inability to perform daily activities such as eating and swallowing, or require temporary discontinuation of acupuncture or rehabilitation sessions; 3. Management requirements: Medical intervention required (e.g., oxygen therapy, medication); symptoms alleviate slowly.

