## Abstract

**Introduction:**

Post-stroke dysphagia (PSD) is a common complication of stroke. Rehabilitation training and acupuncture have been suggested as current effective therapies, but high-quality evidence of acupuncture is insufficient. A meta-analysis has shown that acupuncture may be an effective adjunctive treatment for improving swallowing function, but the guidelines do not provide sufficient recommendations. Therefore, clinical and mechanism-related research on acupuncture treatment for post-stroke dysphagia should be vigorously promoted.

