## Introduction

1

In 2020, the incidence of stroke among adults in China was reported as 310.0 cases per 100,000 person-years (1), and epidemiological projections suggest a sustained increase from 2019 to 2050 (2). Currently, the incidence of post-stroke dysphagia ranges from 37 to 78% (3). Dysphagia can lead to dehydration, malnutrition, aspiration pneumonia, and other complications (4), and may also exacerbate post-stroke mortality and disability (5).

The main treatments for post-stroke dysphagia (PSD) include behavioral interventions, rehabilitative training, pharmacotherapy, and neuromuscular electrical stimulation (NMES) (6). The 2021 AHA/ASA Guidelines for Adult Stroke Rehabilitation (originally published in 2016) suggest that acupuncture may be considered as an adjunctive therapy for dysphagia (Class IIb recommendation, Level B evidence). Clinical studies (7–9) increasingly support the therapeutic benefits of acupuncture in improving swallowing function after stroke (10). Neurophysiological research (11) has clarified the modulatory pathways of the swallowing neural circuit, indicating that acupuncture may act through targeted modulation of this network. These findings provide a mechanistic basis for further research on acupuncture in pathological conditions.

This study aims to evaluate acupuncture’s therapeutic efficacy for post-stroke dysphagia (PSD) by rigorously comparing it with conventional swallowing rehabilitation. Although previous research has demonstrated acupuncture’s potential benefits, direct comparisons with established rehabilitation methods remain lacking. Moreover, the neural mechanisms underlying acupuncture’s effects on PSD require further clarification. Given the substantial differences between acupuncture and rehabilitation procedures in clinical trials, implementing a single-blind design is challenging. Therefore, an open-label, multi-center, randomized controlled trial will be adopted to comprehensively evaluate the efficacy of acupuncture for PSD patients, clarify the neural mechanisms involved in acupuncture intervention for post-stroke dysphagia and obtain high-quality evidence-based data.

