### Objective

2.1

This study aims to explore acupuncture’s efficacy in post-stroke dysphagia (PSD) patients, clarify the neural mechanisms of acupuncture intervention for PSD, and obtain high-quality evidence.

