##### Analysis of adverse events

2.9.3.1

Treatment-related AEs include symptoms such as throat discomfort or pain, coughing, and aspiration pneumonia caused by the trial intervention or acupuncture. Serious adverse events (SAEs) refer to symptoms that result in hospitalization, persistent or significant disability, functional impairment, life-threatening conditions, or death (44). Additionally, there may be treatment-unrelated AEs that occur outside the treatment period (44).

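### The adverse-event attribution rule names post-stroke depression, not dysphagia, as the competing cause, and the table it cites for attribution criteria grades only severity

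*Protocol article*

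**What the plan says.** Section 2.9.3.2 states what attribution must distinguish: events caused by acupuncture on one side, and on the other "those potentially attributable to pre-existing post-stroke depression (PSD), attribution will be determined in accordance with the CIOMS guidelines" and a reporting standard for adverse events in acupuncture trials. It then refers the reader to Table 3 for the detailed criteria.

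Section 2.9.3.1 gives as examples of treatment-related events "throat discomfort or pain, coughing, and aspiration pneumonia caused by the trial intervention or acupuncture". On unrelated events it says only that "there may be treatment-unrelated AEs that occur outside the treatment period".

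The abbreviation is introduced differently in the rest of the article. The Abstract has "Post-stroke dysphagia (PSD) is a common complication of stroke", the Introduction has "The main treatments for post-stroke dysphagia (PSD) include behavioral interventions", and section 2.1 speaks of "post-stroke dysphagia (PSD) patients".

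Three other sections put the rule to use. Section 2.11 requires clinical staff, safety assessors and Safety Committee members to be trained on the attribution criteria. Section 2.9.3.3 has a preliminary attribution level recorded after each acupuncture session. Section 2.9.3.5 promises to report the possible relationship to the intervention for every event.

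**The concern.** An attribution rule is useful only if it names the right rival explanation. Here the rival is depression, which is not an entry criterion and for which the assessment schedule in Table 4 has no dedicated scale. All 100 randomised patients have dysphagia, and the rule does not mention it.

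The events most in need of the distinction are those that both disease and treatment could produce. Of the examples in section 2.9.3.1, the Introduction itself names aspiration pneumonia as a consequence of dysphagia. That coughing can also come from dysphagia is not stated in the article; I take it as an ordinary clinical assumption.

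What is at stake is the reported relationship of events to treatment. Safety is in the trial's title, and relatedness is a reported result. The primary outcome, the sample size and the efficacy analysis are not touched.

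**Working it through.** There is no figure to reproduce, so the check sets the texts side by side.

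1. **Meaning of PSD.** Four sections spell out the abbreviation: the Abstract, the Introduction, section 2.1 and section 2.9.3.2. The first three say dysphagia and only the last says depression. The participants are called PSD patients elsewhere (for example in section 2.2), which makes sense only for dysphagia. The word in section 2.9.3.2 is an error, most likely a mis-expanded abbreviation.

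2. **Could depression be intended?** Section 2.3 does not require it. Table 4 lists FOIS, ReHo, ALFF, sEMG, PAS, YPR-SRS, SWAL-QOL, NIHSS, PRO and TEX-Q, none of which is a depression scale. Mental health appears only as a domain of SWAL-QOL and of the PRO, and severe psychiatric impairment is an exclusion (section 2.4). Nothing suggests that depression was meant as the main alternative cause of throat symptoms, coughing or pneumonia.

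3. **Does section 2.9.3.1 supply the missing contrast?** Only partly. Its examples count as treatment-related on condition that the intervention caused them, so a pneumonia caused by dysphagia falls outside the definition. But the only unrelated events it mentions are those outside the treatment period. It describes no unrelated event during the four weeks of treatment. Follow-up lasts 90 days (section 2.7) and the end-of-treatment assessment is at Day 30 (Table 4), so 90 − 30 = 60 days lie in the period that the sentence associates with unrelatedness.

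4. **Does Table 3 supply it?** No. The table is titled as severity grading, and its rows are mild, moderate and severe. It has no causality category. A reader who suspects a slip in section 2.9.3.2 and turns to the cited criteria finds none. This is a wrong pointer in the printed text, not a detail left to a fuller document.

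5. **Which arms does the rule cover?** The contrast in section 2.9.3.2 names acupuncture alone. Section 2.9.3.1 speaks of the trial intervention or acupuncture, and the control arm receives active swallowing training. One of its exercises (section 2.8.2.2) teaches patients to cough after swallowing, so attribution matters in that arm too.

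**The case against.** The strongest reply is that this is a slip in one word, in a trial where everyone knows PSD is dysphagia, and that the surrounding text protects against harm. Section 2.9.3.1 makes causation a condition of treatment-relatedness. Section 2.9.3.2 defers to two external standards. The form in section 2.9.3.3 records onset, timing relative to the intervention, association with swallowing and an attribution level. The Safety Committee verifies form entries and reviews serious events (section 2.9.3.4).

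Most of this stands, and it limits the consequence. A reader might infer that coughing or pneumonia caused by dysphagia cannot be attributed to anything but treatment. The documents do not support that, because the causal condition, the external standards and the form all leave room for a disease attribution. The content of those standards is not shown, so it cannot be said that they lack a suitable category.

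A reader might also infer that safety conclusions will be wrong in both directions, with early disease events counted as related and late needling events as unrelated. That does not follow either. The timing sentence is permissive: it says such events may occur. It does not say that only late events are unrelated, or that all late events are.

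The reply does not remove the defect. The rule still states the wrong contrast, its pointer still leads to a table without causality categories, and the form is described only for acupuncture sessions.

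**Conclusion.** Wrong as written; minor severity. Section 2.9.3.2 gives staff the wrong contrast and no printed causality categories, and section 2.9.3.1 adds a timing phrase that fits poorly with attribution by cause. The error sits in a rule that staff are trained on and that feeds a reported result, so it should be corrected.

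The size of the effect cannot be computed. The article gives no event rates, and the counts of 100 patients and about 60 post-treatment days describe exposure, not misclassification. The conclusion assumes that depression is a mis-expansion of PSD. If depression really was intended, the omission of dysphagia as a competing cause would remain.

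**What to change.** - In section 2.9.3.2, replace depression with post-stroke dysphagia or the underlying stroke as the competing cause, and widen the contrast from acupuncture to the interventions of both arms.
- In section 2.9.3.1, delete the phrase that places unrelated events outside the treatment period, so that relatedness is judged by causality for every event from Day 0 to Day 90.
- In section 2.9.3.2, replace the pointer to Table 3 with one to the causality categories of the cited standards. Table 3 can stay as the severity scale. Without this step the two wording changes would leave the rule referring to criteria that are not printed.

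The cost is wording, one cross-reference and the matching line in the training material. No new data are needed. Section 2.6 gives recruitment as ending in June 2025, so if events have already been classified, the coughing and pneumonia entries should be checked once against the corrected rule.

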##### Management of adverse events

2.9.3.3

When subjects experience significant AEs, clinicians must document all details and implement appropriate interventions. For SAEs, clinicians should administer emergency measures until the patient’s condition stabilizes. If abnormal laboratory parameters are observed, continuous monitoring should be performed until values normalize, with consideration given to discontinuing observation. Following each acupuncture session, clinicians will document any adverse events (AEs) using an Immediate AE Record Form. The recorded information will include AE symptomatology, time of onset, duration, severity, temporal relationship to the intervention (intra- or post-intervention), association with swallowing actions, and preliminary attribution level. Three days after SAE management, the subject’s general condition should be reassessed with relevant laboratory tests as needed to ensure no impact on subsequent treatment processes and outcomes. Subjects who develop abnormal post-treatment values after having normal pre-treatment values should receive regular follow-up examinations until the follow-up period concludes (Figure 4).

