**FIGURE 2 F2:**
[figure not shown]
Location of acupuncture points (Source: Atlas of meridians and acupuncture points by JiuDaifu).

**TABLE 2 T2:** Anatomical location of selected acupoints.

Acupoints	Location
GB20 (Fengchi)	In the posterior region of the neck, under the occiput, in the depression between the upper part of the sternocleidomastoid muscle and the upper part of the trapezius muscle.
GB12 (Wangu)	On the neck, at the posterior and inferior depression of the mastoid process behind the ear.
TE17 (Yifeng)	On the neck, behind the earlobe, at the anterior and inferior depression of the mastoid process.
CV23 (Lianquan)	In the anterior region of the neck, on the anterior median line, above the laryngeal prominence, and in the depression of the upper edge of the hyoid bone.

Patients will lie in a supine position. GB20 (Fengchi) needles will be bilaterally inserted at a 30° inferior angle toward the thyroid cartilage to a depth of 2.5–3.0 cun (≈65–75 mm). Small-amplitude, high-frequency twisting manipulation will be applied for 1 min to achieve strong stimulation, targeting a throat numbness/swelling sensation called “deqi.” GB12 (Wangu) and TE17 (Yifeng) will be needled with the same depth, angle, and technique as GB20. CV23 (Lianquan) will be inserted to 1.0–1.5 cun (≈25–40 mm) with lifting-thrusting manipulation. All needles will be retained for 30 min. Participants will receive three sessions per week for four consecutive weeks.

Deqi will be assessed subjectively using the Chinese version of the Massachusetts General Hospital Acupuncture Sensation Scale (c-MASS) (20), which evaluates 12 distinct sensations to quantify deqi intensity and quality. Participants will self-complete the c-MASS within 30 s after each needle manipulation. In accordance with prior domestic research (21), “adequate deqi” will be defined as a total c-MASS score ≥ 4, accompanied by at least two typical sensations (soreness, numbness, fullness, or heaviness) each rated ≥ 3. Cases not fulfilling both criteria will be classified as “inadequate deqi.” The Deqi Quality Index (DQI) for each participant will be calculated as the mean of the total c-MASS scores recorded at three time points: initiation of intervention, 15 and 30 min.

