##### Safety analysis

2.9.3.4

Adverse events will be analyzed using standardized evaluation scales. An independent Safety Committee (SC) will be established, composed of five members with no conflicts of interest: a principal investigator, an acupuncture clinician, a rehabilitation medicine specialist, a statistician, and a patient representative from the stroke rehabilitation community. The SC will be responsible for reviewing and evaluating all safety data and adverse events collected during the trial. Its specific duties will include assessing cumulative serious adverse event (SAE) reports, verifying entries in the Immediate AE Record Form within 24 h, conducting routine reviews every 2 months, and performing expedited reviews of any SAE within 48 h to ensure trial integrity and protect participants’ rights and health. For statistical analysis, Fisher’s exact test will be employed for categorical data comparisons, while the Kruskal-Wallis H test will be utilized for analyzing ordinal categorical variables.

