##### Scope of adverse event reporting

2.9.3.5

In accordance with the CIOMS Guidelines for Adverse Event Reporting (45), this study will comprehensively collect and report all adverse events (AEs). The reporting will include the frequency, severity, and potential relationship to the intervention for every documented AE, thereby ensuring a complete representation of participant safety exposure throughout the trial period.

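### The per-session adverse event form is specified only for acupuncture sessions, and the sensation that needling aims for can be graded as a mild event, so non-serious events may be counted unequally between the arms

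*Protocol article*

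**What the plan says.** **Recording.** Section 2.9.3.3 contains two documentation duties. One applies to all participants but is limited to significant events: "When subjects experience significant AEs, clinicians must document all details and implement appropriate interventions". The other is a prompt at every session, and the text attaches it to one treatment: "Following each acupuncture session, clinicians will document any adverse events (AEs) using an Immediate AE Record Form". Section 2.9.3.4 has the Safety Committee verify entries in that form within 24 hours. Section 2.9.3.5 adds that "this study will comprehensively collect and report all adverse events (AEs"), and Table 4 shows an adverse event row running from baseline, not split by arm.

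**Sessions.** Both arms have three sessions a week for four weeks (sections 2.8, 2.8.1 and 2.8.2).

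**Definition.** Table 3 gives as an example of a mild event "transient throat numbness and distension (duration < 30 min"). Section 2.8.1 describes the manipulation at GB20 as "targeting a throat numbness/swelling sensation called" deqi, uses the same technique at GB12 and TE17, and retains the needles for 30 minutes.

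**Attribution.** Section 2.9.3.2 sets out to separate events caused by acupuncture from "those potentially attributable to pre-existing post-stroke depression (PSD"). It refers to Table 3 for the detailed criteria; that table is titled "Severity grading criteria for adverse events".

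**Analysis.** Section 2.9.3.4: "Fisher’s exact test will be employed for categorical data comparisons", with a Kruskal-Wallis test for ordinal categories.

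**The concern.** A between-arm comparison of event counts is interpretable only if events are looked for and defined in the same way in both arms. Here one arm is prompted at every session and the other, so far as the text goes, is not. Rehabilitation is not free of events: section 2.8.2.2 includes supraglottic and effortful swallows, and section 2.9.3.1 names coughing and aspiration pneumonia among treatment-related events. A mild cough after a rehabilitation session could go unrecorded where the same cough after needling would be written down.

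The definition adds to this. Throat numbness produced by needling can arise only in the acupuncture arm. If it counts as a mild event, a sign of adequate treatment becomes a harm in that arm alone.

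The attribution errors do not change total counts. They leave the split into related and unrelated events poorly specified, and that split matters in patients whose underlying dysphagia can itself cause aspiration.

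**Working it through.** **1. What is prompted in each arm.** Section 2.7 gives 100 patients allocated 1:1, so 50 per arm. That figure reproduces: with a difference of 1.31 - 0.31 = 1.00, less the margin of 0.39, SD 1.09, one-sided α 0.05 and power 0.80, n = 2 × (1.645 + 0.842)² × 1.09² / 0.61² ≈ 39.5, so 40 per arm; 40 / 0.8 = 50. Sessions per patient are 3 × 4 = 12. Prompted records are therefore 50 × 12 = 600 in the acupuncture arm, against none described for the same 600 planned rehabilitation sessions.

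**2. Effect of unequal capture.** The documents give neither an event rate nor a capture proportion, so these are assumptions. Let both arms have the same true proportion p of patients with an event, let acupuncture capture all of them, and let rehabilitation capture a fraction c. The chance of a spurious result is the sum of Bin(i; 50, p) × Bin(j; 50, cp) over all pairs (i, j) with a two-sided Fisher p-value of 0.05 or less.

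| True rate p | c = 100% | c = 75% | c = 50% | c = 25% |
|---|---|---|---|---|
| 10% | 1.8% | 2.6% | 6.3% | 15.9% |
| 20% | 2.8% | 6.0% | 19.5% | 50.8% |
| 30% | 3.1% | 9.5% | 35.4% | 78.3% |

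At p = 20% and c = 50%, the expected counts are 50 × 0.20 = 10 patients against 50 × 0.10 = 5. When c is below 100%, nearly all of the spurious results go against acupuncture (5.8 of the 6.0 percentage points at p = 20%, c = 75%).

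**3. Effect of counting the needling sensation.** Assume full capture in both arms, with a fraction q of acupuncture patients who have no other event counted for the sensation alone. The recorded acupuncture rate is p + (1 - p)q. At p = 20% and q = 25% this is 0.20 + 0.80 × 0.25 = 40%, against 20% in rehabilitation.

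| True rate p | q = 10% | q = 25% | q = 50% |
|---|---|---|---|
| 10% | 16.0% | 73.9% | 99.9% |
| 20% | 10.9% | 51.5% | 98.2% |
| 30% | 7.8% | 36.3% | 93.1% |

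**4. Both together.** With c = 50% and q = 25%, the chance is 94.1%, 92.7% and 92.9% at p = 10%, 20% and 30%.

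**5. With the repair.** With equal recording and the sensation not counted (c = 100%, q = 0), the chance is 1.8-3.1%, within the nominal 5%.

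**6. Attribution.** This needs only reading. Table 3 has three severity grades and no causality category. PSD means post-stroke dysphagia in the title, abstract and objectives, and depression only in section 2.9.3.2.

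**The case against.** The strongest reply is that the text does not address recording after rehabilitation sessions; it does not exclude it. Section 2.9.3.5 promises that every event is collected, Table 4 follows events in all patients, section 2.9.3.1 covers events from the trial intervention as well as from acupuncture, and Table 3 mentions interruption of rehabilitation sessions. The adverse event flowchart (Figure 4) and the full protocol are not shown. This stands as far as it goes: a reader might infer that rehabilitation events will go unrecorded and that the comparison is certainly biased, and the documents do not support that. But a general pledge is not a matching procedure. The article chose to specify the per-session prompt and its verification, and named one arm.

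A reader might also infer that there is no attribution rule at all. That goes too far. Section 2.9.3.2 cites two external standards, the form in section 2.9.3.3 records a provisional causality level and any link with swallowing, and section 2.11 trains staff on the criteria. What fails is the pointer to Table 3 and the expansion of PSD.

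Nor does the text show that nearly every acupuncture patient would be counted as having a mild event. Table 3 gives an example for grading, deqi is already recorded on the c-MASS, and the plan expects some patients with inadequate deqi. The overlap between the two passages remains.

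Finally, the possible effect can be small: at a 10% rate and 75% capture, the spurious rate of 2.6% is still below the nominal level.

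**Conclusion.** The point holds as a risk of unequal ascertainment and definition in the plan as written. For non-serious events, both mechanisms would most likely work against acupuncture. Serious events have a 48-hour committee review that is not tied to an arm, and should be less affected.

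The size cannot be found from the documents. Under assumed equal true rates of 10-30% and 50 patients per arm, unequal capture alone gives a spurious Fisher result in about 3-10% of trials at 75% relative capture and 6-35% at 50%. Counting the intended sensation could add more, depending on how often it is recorded as an event. These figures also take the Fisher comparison to be between the two treatment arms, which section 2.9.3.4 does not state but is the natural reading.

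The two errors in section 2.9.3.2 are certain but are errors of drafting. This should be corrected because safety is in the trial's title and the repair is cheap; it does not undermine the efficacy comparison.

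**What to change.** 1. In sections 2.9.3.3 and 2.9.3.4, specify the Immediate AE Record Form and the 24-hour verification after every session in both arms. If that is already the practice, say so.
2. Reconcile section 2.8.1 with Table 3, so that expected transient deqi recorded on the c-MASS is tabulated separately from adverse events.
3. In section 2.9.3.2, change depression to dysphagia and replace the pointer to Table 3 with the actual attribution categories.
4. The recruitment window in section 2.6 ran to June 2025, so data may already exist. If the form was used in one arm only, report all adverse events and state the unequal ascertainment as a limitation. Rest the between-arm comparison mainly on serious events and others ascertained in the same way in both arms. Do not discard events recorded at acupuncture sessions: that could understate harm.

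The cost is a short existing form at up to 600 rehabilitation sessions, the matching verification work, and changes of wording. The c-MASS is already collected.
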